
D.5.2.5. Second post-test counseling session:  Women in the intervention arm will have a second post-test counseling session that coincides with their 6-week post-partum visit to the Clinic. For many women, a single post-test session is not sufficient to address the numerous challenges that she faces having just learned her HIV serostatus.  This second post-test counseling session captures women several weeks after learning her HIV serostatus.   The opportunity for a second post-test counseling session is critical in order to review some of the important issues related to disclosure and risk reduction that the counselor and the women discussed in the first post-test counseling session, at a time when women may have overcome the initial emotional crisis associated with learning her HIV serostatus.  This counseling session will be an opportunity for HIV-positive women to talk with counselors about their infant feeding experiences and discuss any challenges that they may face in implementing their feeding choices.  This counseling session will add a focus on legal education and referral.  Counselors will introduce women to the idea of legal rights and talk about recourse options with women through the use of vignettes.  UKZN's Campus Law Clinic will work with our team to develop 5 vignettes that describe the most common legal needs o HIV+ women and women at risk for HIV and the legal options that are available to women in those situations.  In the counseling session, the counselor will read the vignette with women.  The vignettes will be a stepping stone to a discussion about the women's own legal concerns and needs. If a woman identifies a legal need, she will be referred to our partners from the Campus Law Clinic, who will be providing legal services at the clinic as a component of post test support. This session will also add a focus on partner testing.  Counselors will ask women about their partner's attitudes and experiences with HIV testing.  Counselors will describe the benefits to partner testing, and assess the barriers that women face to encouraging partner testing.  Counselors will work with women for whom disclosure is a safe alternative to develop plans for discussing testing options with their partners, including the option to test through the Umlazi Clinic.  This session will be another important opportunity to link women to the post-test support groups facilitated by our staff psychologist.

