D.5.2.6 Third post-test counseling session:  The third and final post-test counseling session will coincide with women's 10-week post-partum visit to the Umlazi Section D Clinic. This visit will be another opportunity for counselors to check in with women regarding their decisions and experiences with disclosure, infant feeding, risk reduction, partner testing and legal needs.  Counselors will explore the risk reduction plans that women articulated in their first post-test counseling session and ask them about barriers that they may have faced in implementing their plans. This will be another opportunity for counselors to discuss and practice condom use skills.  This session will add a focus on family planning for both HIV-positive and HIV-negative women. The family planning counseling that will be provided to women will adhere to best practices outlined by UNAIDS92 and WHO93,94.  Helping clients make and implement an informed decision is the goal of the family planning counseling that will be provided to women.  Informed choice has two elements in family planning practice; first clients have the right to make their own choices and second clients need information and advise to help them make these choices.  The role of the counselor is to provide information, support and encouragement for women's choices regarding contraception and family planning.  Counselors will assess women's future fertility intentions, their desire for contraceptives, and the perceived barriers to utilizing contraceptives with their sexual partners.  Counselors will assess women's understanding of different contraceptive options and clarify any misunderstandings that women may have.  Counselors will introduce women to a range of contraceptive options and discuss the efficacy, ease of use, benefits and risks of each option. Counselors will spend time in this session talking and role playing the challenges women face in negotiating contraceptive use in their relationships. Counselors will spend additional time with HIV-positive women who have opted to exclusively formula feed their infants talking about the risk of pregnancy in the absence of breastfeeding.  

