D.8.1.2.  Correct Condom Use:  The consensus recently has been to include measures of both correct and consistent condom use for a more robust behavior change evaluation.72 To measure correct condom use we will ask women to recall during the last sexual encounter in which they used condoms whether they and/or their partner performed the following discrete steps:  1) checked the condom's expiration date; 2) whether their partner had inserted his penis prior to putting on a condom; 3) whether they left space at the tip of the condom; 4) removed air from the tip of the condom;  and 5) whether they or their partner held the rim of the condom on withdrawal. We will calculate the proportion of women who report that they performed all five steps correctly.   

D.8.1.3.  Consistent Condom Use:  Consistent condom use has been selected as a primary outcome based on demonstrated effectiveness in reducing sexually transmitted HIV infection.102,103 104  To measure consistent condom use we will use the Partner grid included in Appendix 12.  In completing this grid, we will ask women about each of their sexual partners, how many times they have engaged in sex with these partners in the last 30-days and how many of these times they used a condom. We will calculate the number of unprotected sex acts by subtracting the number of times a condom was used from the number of sex acts.  

D.8.1.4 Partner uptake of HIV VCT: We will monitor the demand for HIV testing by partners of women in both arms of the study.  We will focus on the primary partner of women, as defined by a partner that they have been with for at least 6-months.  This is a definition that we have used in previous studies and one that we feel will capture the majority of stable primary partnerships in this population of women.  At baseline we will ask all women whether their partner has ever tested for HIV. At the post-intervention assessment we will ask women whether their partner has been tested for HIV since their enrollment in the study.  We are interested in partner uptake of HIV testing at any VCT clinic, not exclusively within the Family clinic.  We recognize that the most accurate rate of HIV VCT uptake by partners would be achieved by asking the partners directly. However, we do not want to compromise the safety and confidentiality of women by contacting their partners for interviews.

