D.8.1.12. Partner Violence: From our previous research, we found that using specific behavioral events rather than a cover term such as 'physical violence' is more useful for the measurement of violence.  This has been corroborated by violence research from other settings, including South Africa47,110  We will measure sexual and physical violence using an adaptation of the Conflict-Tactic Scale111.  (See Appendix 13)  We adapted this scale for use in the research that we conducted in Tanzania and the scale demonstrated good internal consistency and reliability for physical and verbal abuse in this setting60 .  The modified scale demonstrated good reliability and internal consistency in the eight countries where WHO conducted a study on women's health and gender-based violence and in a South African study conducted by Jewkes112,47.  At baseline we will ask women to recall their experiences with violence during pregnancy and prior to pregnancy. At the post-intervention assessment we measure women's experiences with violence in the 9-month period of time since testing.  We will adhere to WHO ethical and safety guidelines for conducting research on violence against women.  We will have a referral list of social and legal services available to women who report current  violence113.

D.8.2. Secondary Outcomes
D.8.2.1. Length of time for counseling sessions:  Counselors will maintain a counseling log form for every woman in the intervention and the comparison arm.  Among other things reported on this log form, counselors will report the beginning and ending time of each counseling session.  

D.8.2.2 Ongoing counseling: We will monitor the ongoing use of counseling services by women in both arms.  Counselors will record every counseling session that is conducted with clients on the counseling log forms.  Through these counseling logs forms we will also track the number of women who return for counseling with her partner. We will start a separate counseling log for those partners who return to the clinic either on their own for HIV counseling or with their partner.  

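### Partner uptake of HIV testing is reported by the woman, and the protocol does not consider that the error in her report may differ between arms

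*Protocol*

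**What the plan says.** Partner uptake is listed among the primary outcomes (Protocol D.8.1). It is named in Aim 2.1 for HIV-positive women and is part of hypothesis H1 in D.11. At follow-up, per D.8.1.4, "we will ask women whether their partner has been tested for HIV since their enrollment in the study". A test at any site counts: "We are interested in partner uptake of HIV testing at any VCT clinic, not exclusively within the Family clinic".

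The same section acknowledges a limit, "We recognize that the most accurate rate of HIV VCT uptake by partners would be achieved by asking the partners directly", and gives the reason for accepting it: "we do not want to compromise the safety and confidentiality of women by contacting their partners for interviews". It does not discuss whether the error could differ between arms.

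Content that bears on what a woman knows about her partner's testing:

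- **Intervention, 6 weeks (D.5.2.5):** "Counselors will ask women about their partner's attitudes and experiences with HIV testing". For women who can disclose safely, counselors also help "to develop plans for discussing testing options with their partners".
- **Intervention, 10 weeks (D.5.2.6):** counselors "check in with women regarding their decisions and experiences with disclosure, infant feeding, risk reduction, partner testing and legal needs".
- **Intervention, first post-test session (Table 1 of intervention components):** detailed disclosure plans, disclosure role-plays and the option of mediated disclosure.
- **Comparison, 6 and 10 weeks (D.7):** sessions of similar length on infant health. Partner testing is discussed if the woman raises it.
- **Both arms, first post-test session (same table):** partner referral for testing and discussion of disclosure plans under the CDC/WHO protocol.

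D.8.2.2, a secondary outcome, sets up a "separate counseling log for those partners who return to the clinic either on their own for HIV counseling" or together with the woman. D.8.1.4 does not refer to it.

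**The concern.** A woman can report a partner's test only if she knows of it. Error of the same size in both arms would mainly dilute a real difference. Error that is smaller in one arm can create a difference where none exists. One arm is prompted, before the outcome is assessed, to ask and talk about the very fact that the woman later reports. Matching the length of the 6- and 10-week sessions, as D.7 does, equalizes contact time but not this prompt.

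At stake is how a positive result on this component of H1 would be read. With the outcome as defined, more testing and more talk about testing look alike. For receipt of ARVs, D.8.1.6 compares self-report with clinic records. D.8.1.4 states no check for partner testing.

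**Working it through.** **1. The plan's own figure.** Table 4 (D.9.3) gives 0.25 versus 0.36 for partner uptake in HIV-positive women, with 279 per arm, two-sided alpha 0.05 (D.9.2) and a normal approximation. Power is not stated. At 80%, the pooled-variance formula reproduces all six cells of Table 3, so 80% is used here.

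n per arm = [1.96 × √(2p̄(1−p̄)) + 0.842 × √(p₁(1−p₁) + p₂(1−p₂))]² / d², with p₁ = 0.25, p₂ = 0.36, p̄ = 0.305 and d = 0.11.

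This is [1.96 × 0.651 + 0.842 × 0.646]² / 0.0121 ≈ 274 per arm. With 279 per arm, power is 80.7%. The 11-point figure stands.

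**2. Smallest significant difference.** With 25% reported in the comparison arm and 279 per arm, an observed difference of about 7.6 points gives z ≥ 1.96: the standard error is √(2 × 0.288 × 0.712 / 279) ≈ 0.0383, and 0.076 / 0.0383 ≈ 1.98.

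**3. False difference from knowledge alone.** Let T be the true uptake, equal in both arms, and k the probability that a woman knows of and reports a test that took place. Then:

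reported rate = T × k, and false difference = T × (k_int − k_comp).

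The protocol gives no value for k, and every k below is an assumption. T is set to the two rates in Table 4, also as an assumption.

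| T | k_comp | k_int | Reported, comparison | Reported, intervention | False difference |
|---|---|---|---|---|---|
| 25% | 0.7 | 0.8 | 17.5% | 20.0% | 2.5 points |
| 25% | 0.8 | 0.9 | 20.0% | 22.5% | 2.5 points |
| 25% | 0.7 | 0.9 | 17.5% | 22.5% | 5.0 points |
| 36% | 0.7 | 0.8 | 25.2% | 28.8% | 3.6 points |
| 36% | 0.8 | 0.9 | 28.8% | 32.4% | 3.6 points |
| 36% | 0.7 | 0.9 | 25.2% | 32.4% | 7.2 points |

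The range is 2.5/11 = 23% to 7.2/11 = 65% of the difference in Table 4.

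**4. Effect on the error rate.** Take T = 36% and hold the comparison arm's reported rate at Table 4's 25%, so k_comp = 0.25/0.36 = 0.694. A 10-point gap in k gives 25.0% versus 28.6%, and the chance of a significant result is about 16%. A 20-point gap gives 25.0% versus 32.2% and about 47%. The nominal rate is 5%.

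**5. A smaller case.** Suppose knowledge rises only through the disclosure gain in Table 4 (25% to 36% in HIV-positive women). Then the false difference = T × 0.11 × (k if disclosed − k if not). With assumed pairs of (0.9, 0.5), (0.8, 0.4), (0.9, 0.3) and (1.0, 0.2), and T of 25% to 36%, it runs from 0.25 × 0.11 × 0.4 = 1.1 points to 0.36 × 0.11 × 0.8 = 3.2 points.

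**The case against.** The strongest reply has four parts.

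- **The arms differ less than they seem to.** Both receive CDC/WHO partner referral and disclosure discussion at the first post-test session. Clinic patients are in any case invited to bring partners for testing (D.2.1), and D.7 obliges counselors to respond when comparison women raise the subject. This stands, and it argues for a modest knowledge gap.
- **The limitation is acknowledged and justified.** D.8.1.4 gives safety and confidentiality as the reason for not asking partners. This also stands. A reader might infer that partners ought to be interviewed; nothing here supports that, and the fix does not need it. The acknowledgement does not, however, cover error that differs by arm.
- **The sizes are assumed.** This stands. No scenario in the step 3 table reaches the 7.6-point threshold in expectation, although the chance of a false positive still rises. The T = 25% rows also imply comparison-arm reports of 17.5% to 20%, below Table 4's 25%.
- **The survey is not shown.** A 'does not know' answer may already exist, and D.3 and D.8 plan cognitive interviews and re-piloting that name partner uptake. How such answers are analyzed may be left to a statistical analysis plan. Fair, but an item that is not asked cannot be recovered later, so data capture has to be settled now.

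A reader might also think that the partner log could decide the matter, with an effect claimed only if the log agrees. It cannot. It records counseling at one clinic, whereas a test anywhere counts. Intervention women are offered mediated disclosure at the clinic and helped to plan partner testing that may take place there, so the log may itself tilt toward that arm. Agreement could reflect a shift of place, and disagreement could reflect real testing elsewhere.

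**Conclusion.** The point holds as a cheap improvement to how a primary outcome is measured and labeled. D.8.1.4 rests on the woman's report, and the protocol concedes lower accuracy without considering that it may differ by arm. The content of the sessions makes such a difference plausible.

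A reader might infer that intervention women will certainly know of more partner tests, or that a positive result would be an artifact. The protocol supports neither: it has no data on women's knowledge, and both arms receive some partner-testing and disclosure content. If true uptake is equal at 25% to 36% and knowledge differs by 10 to 20 points, the false difference is about 2.5 to 7.2 points against the 11 in Table 4. If knowledge rises only through disclosure, it is about 1 to 3 points. All of these rest on assumed k and T, and on no woman reporting a test that did not happen.

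**What to change.** In D.8.1.4:

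1. Record 'does not know' as a separate answer and report its frequency by arm.
2. Add one item for women who report a test: how she knows (they tested together, he told her, she saw the result).
3. Label the outcome woman-reported partner testing, here and in H1.
4. Report a sensitivity analysis that bounds the arm difference: 'does not know' counted as tested and as not tested, including opposite extremes in the two arms, and the comparison repeated by source of knowledge. These bounds do not reach women who answer no in error, so they limit the problem and do not remove it.
5. If the partner log of D.8.2.2 is shown beside this outcome, present it as descriptive support only, with no rule that a claim depends on it.

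The cost is two survey items and one sensitivity analysis. No partner is contacted, and the changes fit the refinement and re-piloting of this measure already planned in D.8.

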
B.2. Low uptake of PMTCT programs by women is a major barrier to their implementation.  Several PMTCT clinical trials have demonstrated a 37-50% reduction of MTCT using a short course of zidovudine9-11 and/or nevirapine12.  The establishment and scaling up of PMTCT programs in resource-constrained settings is a high priority for many funding agencies.  In 2002, President Bush launched the $500 million Mother-and-Child HIV Prevention Initiative designed to prevent mother-to-child transmission.  Rapidly scaling up PMTCT services is a key objective of the President's $15 billion PEPFAR initiative, with South Africa being one of the countries in sub-Saharan Africa designated to receive funds.1  However, there are a number of barriers to women's participation in PMTCT programs that may limit the widespread success of these programs.  In a wide range of African settings women's low uptake of PMTCT programs remains a persistent challenge.13-17  In order to benefit from interventions that can reduce mother to child HIV transmission women must be willing to be tested for HIV, and if they are HIV infected they must also be willing to accept and adhere to available ARV prophylaxis.  The experience of KwaZulu-Natal in rolling out PMTCT programs illustrates the way in which women's low uptake of PMTCT services compromises the program's ability to achieve their desired outcomes.  A total of 233,074 pregnant women received pre-test counseling for the period between June, 2001 through March, 2004, of whom 179,211 (77%) volunteered to test for HIV.  Of those who tested, 35% were HIV-positive.  Among both HIV-positive and HIV-negative women, approximately 90% received their HIV test results through post-test counseling.   Of the women who tested positive only 58% were issued with a single dose of NVP at the antenatal clinic.  In a report developed by the director of the KwaZulu-Natal (KZN) Provincial PMTCT program, [name] (the co-PI on this study), the major challenge to implementing the PMTCT programs in all sites was the sub-optimal uptake of ARVs.  The KZN PMTCT report concludes that women need ongoing support to overcome barriers to enrolling in PMTCT programs.    

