PMTCT program.  Most women starttheir ANC visits at 28-weeks gestation, and women are usually offered testing at their first visit. Women are given standard HIV post test counseling according to WHO/CDC guidelines in the form of group counseling with 8-10 other women from the ANC clinic. Those who agree to be tested are tested for HIV according to the standard HIV testing algorithm used in the antenatal clinic. A participant provided a blood specimen from a finger prick for a rapid HIV test (Determine: Abbott Laboratories, Abbott Park, IL). If a reactive result was obtained with the Determine rapid HIV test, the participant's HIV status was confirmed with a second rapid test (Smart Check (WDI). In instances where a specimen was reactive to the Abbott kit, but negative on the SmartCheck, a blood specimen was sent for confirmation by an ELISA performed at the Department of Virology, University of KwaZulu-Natal.  All women are given standard HIV post-test counseling.  HIV infected women are: counseled on safe infant feeding options, allowed to make an independent choice on their preferred infant feeding method, given further information and support regarding their infant feeding choice, and have access to free formula if they opt to use replacement feeding. HIV-positive women are also offered a single dose of NVP according to the HIVNET 012 protocol. The drug is dispensed to women at 32-weeks of gestation.  All HIV-infected women receive an intrapartum dose of NVP (200mg) for self-administration at the onset of labor. When these women arrive at the hospital they are asked by the midwife in the labor ward whether she has taken her NVP dose. If women have not taken the dose then it is administered at that time.  All infants born to HIV-infected women receive a single dose (6mg if weighing 2kg or more and 2mg/kg for those weighing less than 2kg) of NVP within 24-hours of birth.  It is possible that changes to the nationally approved recommended regimen for ARV prophylaxis will occur during the course of the study, reflecting improvements in the standard of care in South Africa and concerns over resistance to Nevirapine among pregnant women. Should this happen we shall carefully document and track such changes. It should be noted that since this will occur consistently in both study arms randomization will help to control for any resulting biases from such a change in ARV regimen.   Women are invited to bring their partners in for testing.  After delivery, all post-partum women bring their babies for follow up according to the Expanded Program on Immunization (EPI) schedule at 6,10, and 14 weeks and 6,9 and 15 months to the PHC Clinic.     

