D.4.8.   Medical chart review: As women's antenatal care records cards are kept at the hospital following delivery, it is necessary for our research nurses to extract specific clinical information for individual study files to provide continuous care following delivery. The medical chart extraction form will include operational and clinical information. Operational information will include items like the length of time of each of the sessions and receipt of ARV or prophylaxis. Medical history information that will be extracted is all information that would normally be gathered during a typical ANC or post delivery visit and includes items like gestational age, pregnancy history, STI history, HIV test result, infant feeding intention, receipt of ARV prophylaxis and contraceptive use. All of the counselors, clinic and research staff, will be trained in how to log the length of the interview sessions on this form.  Medical charts extraction forms will be reviewed 4 times during the study period, shortly after the 1, 2nd and 3rd post-test counseling visits, and at the very end shortly before the 9-month post-partum assessment. This information will be collected by our research nurses and recorded on the chart extraction form. The information will then be entered into our data base by our data capturer.  

D.4.9. In-Depth Interviews with Subset of Women:  Among those women who are randomized to the intervention arm and who return for their 9-month follow-up assessment, we will interview qualitatively a subset of 20 women who have disclosed HIV test results to their sexual partners, and 20 women who have not disclosed results to her sexual partner. The purpose of the qualitative interviews is to explore in more depth women's experiences with several of the study outcomes including infant feeding, family planning, and sexual behavior change. The data from these interviews will be triangulated with data from the post-intervention surveys to gain a more complete understanding of the processes that underlie changes in behavior and decisions that women make.  These women will be systematically selected based by their response to the question on HIV serostatus disclosure from the survey interview. Survey interviewers will ask every 3rd woman who has and has not disclosed to sexual partners whether she would be willing to participate in an additional interview until we have recruited 20 women from each category for these interviews. 

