D.8.Behavioural and clinical Assessments:  The survey instrument will be developed following standard practices.  The items will be written in Zulu, pre-tested on a few respondents, exit interviews will be conducted to determine if the content was understood as expressed, changes made, and then the survey will be translated into English by an independent translator to determine whether the content remains as planned.  Alterations will then be made, back-translated into Zulu and then pre-testing will be conducted a second time, with approximately 20 representative respondents.  Scales and variables that will be used to measure the key study outcomes such as emotional distress, social support, MTCT acceptance, and partner uptake of VCT will go through another version of refining and re-pilot testing with an additional 20 women. See Appendix 11 for a table of constructs, variables and measures to be used in the survey assessments.  The instrument development will take place during the phase of ethnographic research.  

D.8.1. Primary Outcomes
D.8.1.1. STI Incidence:  Incidence of STIs will be measured and compared among women in the intervention and control arms. Women are screened for a range of STIs upon enrollment to the ANC clinic including (Neisseria gonorrhea, Trichomonas vaginalis, Syphilis, and Chlamydia trachomatis) at baseline.  All women who test positive for any STI are treated immediately.   For the purpose of our study we will measure incidence of Neisseria gonorrhea, Trichomonas vaginalis, and Chlamydia.  These three organisms offer advantages in the evaluation of behavior change interventions in that they are curable with a single-dose treatment regimen and they are sufficiently prevalent in the target population to warrant inclusion.101  All women who return for the follow-up visit 14 weeks post-partum will be re-screened for Neisseria gonorrhea, Trichomonas vaginalis and Chlamydia. All women in the intervention and control arms who are screened for STIs at 14 weeks, will also have a PAP smear done at the time of the cervico-vaginal examination.  Women found to have an STI at this visit will be treated at that visit.   We feel it is important to include a biological outcome as one of our primary study outcomes to measure intervention efficacy. This will enable us to triangulate our findings from self-reported risk behavior data we gather from the women to gain a more complete understanding of behavior change.72  

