D. 8.1.5:  Acceptance of HIV VCT: The clinic nurses indicate in every woman's file whether HIV testing was accepted or declined.  We will end up enrolling and collecting baseline data on some women who opt not to test for HIV. Women who are enrolled but decline HIV testing will receive ongoing antenatal care and offered the opportunity to test for HIV at subsequent visits. The data that we have from the baseline interview will allow us to compare demographic and risk characteristics among women who accept HIV VCT with women who decline HIV testing. We will also be able to measure the effect of the intervention on women who initially refuse to test for HIV at baseline, by comparing HIV testing outcomes in the intervention and control arms.

D.8.1.6. Receipt of ARV Prophylaxis:  We will measure receipt of ARVs by asking women at the 14 weeks post-partum follow-up assessment whether they received the dose of NVP offered through the ANC clinic.  The clinic keeps records in every woman's file on whether she has received NVP.  We will compare the self-reported rates of acceptance from our survey with the rates that are recorded in the clinic records.  

D.8.1.7. Adherence to national infant feeding guidelines: We will measure infant feeding choices by asking women to recall whether in the first six months post-partum they practiced exclusive breastfeeding, exclusive replacement feeding or mixed feeding.  Reports of either exclusive breastfeeding or exclusive formula feeding will be considered in adherence with national guidelines. Reports of mixed feeding will be considered non-adherence to national guidelines. 
  
D.8.1.8. Family planning use:  At the 14 week and 9-month follow-up assessment we will ask women whether they are currently using any contraceptive method.  We will calculate the proportion of women who are currently using any contraceptive method including female sterilization (performed in the past 14 weeks or 9-months), pill, IUCD, injectables, male condom, female condom, or periodic abstinence, withdrawal, emergency contraception.  

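### D.8.1.6 rests ARV receipt, a primary outcome, on self-report at 14 weeks by women who know their arm, and uses the clinic record only for a comparison of rates

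*Protocol*

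**What the plan says.** Section D.8.1.6 stands under "D.8.1. Primary Outcomes" and fixes the measure: "We will measure receipt of ARVs by asking women at the 14 weeks post-partum follow-up assessment whether they received the dose of NVP". It continues: "The clinic keeps records in every woman's file on whether she has received NVP". The stated use of that record is a cross-check: "We will compare the self-reported rates of acceptance from our survey with the rates that are recorded in the clinic records". No sentence says which source decides the outcome when the two differ, or what happens for a woman with no 14-week survey.

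The record is also planned study data. D.4.8 (Medical chart review) says: "Operational information will include items like the length of time of each of the sessions and receipt of ARV or prophylaxis". The same section lists, among the clinical items to extract, "infant feeding intention, receipt of ARV prophylaxis and contraceptive use". The consent text in section E tells women that this item will be taken from their charts.

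On timing, D.2.1 says: "The drug is dispensed to women at 32-weeks of gestation". On knowledge of arm, D.4.4 has each woman open her own colour-coded card. D.5.2.1 describes a video, shown only to the intervention arm, that is meant to encourage PMTCT participation and in which both HIV-positive characters accept ARVs. D.5.2.3 adds ARV counselling in that arm on fears and barriers.

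**The concern.** The outcome is a discrete event that the clinic documents near the time it happens. The protocol instead takes it from a face-to-face interview months later. The respondent knows her arm and, in one arm only, has received extra encouragement to accept the drug. If intervention-arm women who did not receive the drug are more inclined to say that they did, the self-reported rate rises in that arm without any change in receipt, and it does so on a primary outcome.

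The self-report also exists only for women who attend at 14 weeks. An analysis that follows D.8.1.6 literally has no value for the others, although a clinic file exists for them.

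The choice is not explained. D.8.1.5, directly above, relies on the clinic file for acceptance of HIV testing. D.8.1.4 accepts a less accurate source for partner testing but gives women's safety as the reason. D.8.1.6 gives no reason, and since the chart item is already covered by consent, the reason used for partner testing does not carry over.

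**Working it through.** **1. Inputs from the protocol.** HIV-positive women: 279 per arm (D.9.3). ARV receipt: .58 to .69, 11 points (Table 4). Two-sided alpha: 0.05 (D.9.2). Loss: about 10% (D.9.3, D17). Power is not printed as a number; 80% is assumed.

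**2. Reproducing the plan's figure.** The pooled normal approximation is

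n = [1.96·√(2p̄(1−p̄)) + 0.842·√(p1(1−p1)+p2(1−p2))]² / (p1−p2)².

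For STI incidence .22 vs .13, p̄ = .175 and n = (1.053 + 0.449)² / 0.0081 ≈ 279, as in Table 3. The other five cells of Table 3 also reproduce at 80% power. For .58 vs .69 the same formula gives 300 per arm, and 279 per arm gives 77.1% power. The ARV row of Table 4 therefore holds only to rounding.

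**3. Delay.** Dispensing at 32 weeks' gestation, birth assumed at 40 weeks, survey at 14 weeks post-partum: 40 − 32 + 14 = 22 weeks.

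**4. Differential over-reporting (rates assumed, not in the protocol).** Take true receipt as 58% in both arms. If a share k of the 42% non-recipients says yes falsely, the reported rate is 0.58 + 0.42k. The spurious difference is d = 0.42(k1 − k0). The chance of a significant result is Φ(d/SE − 1.96) + Φ(−d/SE − 1.96), with SE from the two reported rates at 279 per arm.

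| k0 control | k1 intervention | Reported rates | d (points) | P(reject) |
|---|---|---|---|---|
| 10% | 10% | .622 vs .622 | 0 | 5% |
| 5% | 10% | .601 vs .622 | 2.1 | 8% |
| 5% | 15% | .601 vs .643 | 4.2 | 18% |
| 5% | 25% | .601 vs .685 | 8.4 | 55% |

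Example, second row: SE = √(.601·.399/279 + .622·.378/279) = .0413; d/SE = 0.51; P = .073 + .007 = .080.

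**5. Attrition (return rates assumed).** Suppose 95% of recipients and 83% of non-recipients return in both arms. The rate among attenders is .58·.95 / (.58·.95 + .42·.83) = .612 in each arm: the level is too high, but the difference is 0. If non-recipients return at 83% in control but 95% in intervention, the rates are .612 and .580, a difference of −3.2 points, against the intervention.

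**6. Precision.** If 279 per arm are the returners after 10% loss, 279/0.9 = 310 were randomised. Power for .58 vs .69 is 77.1% with 279 and 81.3% with 310.

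**The case against.** The strongest reply is that the protocol plans both sources and compares them. A reader might infer from the first sentence of D.8.1.6 that self-report replaces the record and that non-attenders are lost. The documents do not support that: the record is extracted and compared, and nothing says that non-attenders' chart data are discarded. If the comparison were tabulated by arm, it would expose differential over-reporting. Rules for discordant sources could also be left to a statistical analysis plan, which is not at hand. This narrows the point but does not remove it, because the protocol itself names the source of a primary outcome and names the weaker one.

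Two other strong readings fail. The first is that attrition mimics an intervention effect. D.9.3 expects consistent attrition across arms after results are returned, equal patterns leave the difference unbiased, and unequal ones can act against the intervention. The second is that the planned outcome is not the variable that was powered. The .58 base rate does match a programme figure in B.2 ("Of the women who tested positive only 58% were issued with a single dose of NVP at the antenatal clinic"), but the event is the same and only the data source differs.

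It is also fair to say that the over-reporting rates are assumptions. Table 1 gives comparison-arm women PMTCT and ARV information too, so some false reporting there is plausible; the scenarios allow for it.

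Finally, the record is not free of problems. D.4.8 says that antenatal cards stay at the hospital after delivery, and it does not state that charts of 14-week non-attenders are extracted. Extraction is by research nurses, who under D.5.2.8 also deliver intervention content and so are not blinded. These limits stand and belong in the fix.

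**Conclusion.** The point holds as a poorly chosen measurement rule. A primary outcome is defined by recall about 22 weeks after dispensing, from attenders only, by women who know their arm, while a record for every woman is given only a comparison role.

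The size of any bias is unknown. Under the assumed false-yes rates it runs from about 2 points (8% false positives) to about 8 points (55%), against a planned difference of 11 points; with equal over-reporting there is none. Attrition on its own mainly affects the level and, if the 10% loss assumption is right, costs about 4 points of power (77.1% against 81.3%). The protocol should correct this, but it does not by itself invalidate the trial, since the data needed for the better definition are already planned.

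**What to change.** In D.8.1.6, define the outcome as receipt recorded in the clinic file, taken from the D.4.8 extraction form, for all randomised women who tested HIV-positive, whether or not they attend at 14 weeks. Keep the 14-week self-report as a supporting analysis, and tabulate its agreement with the record by arm.

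In D.4.8, state that charts of 14-week non-attenders are extracted as well.

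State whether the outcome counts only a dose issued through the ANC clinic, as the D.8.1.6 question suggests, or also one first given in the labour ward, a route that D.2.1 describes separately.

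The cost is a change of wording plus some added extraction effort for non-attenders. The downsides are some incomplete charts, extraction by nurses who know the arm, and a record that shows receipt and not ingestion. Since the outcome is named as receipt, the last limit is acceptable.
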